**Fig. 2 Fig2:**
[figure not shown]
Diagram showing the course of the study

During the intervention phase, the hospital pharmacist will be in charge of admission and discharge medication reconciliation, 3 pharmaceutical interviews, therapeutic follow-up and communication with the CP. Moreover, he/she will conduct 3 pharmaceutical consultations with the outpatient 1 month (M1), 3 months (M3) and 12 months (M12) after transplantation. To standardize this intervention over the various hospitals, hospital pharmacists will receive a 2-day training in medication reconciliation procedures, pharmaceutical interviews and consultations and therapeutic follow-up by an experienced clinical pharmacist who is accredited by the SFPC. Investigators (i.e. hospital pharmacist) from each centre will be trained at the sponsor centre (Tours University Hospital). Support documents (e-learning, support sheet for conducting pharmaceutical interviews, pharmaceutical consultations, drug reconciliations, standard letters to the attending physician, immunosuppressive drugs tryptic, checklist for CP, etc.) will be given to the trained centre. Each document will have been previously adapted to the current practices of the trained centre and validated by the latter. This training will take place in the 7 weeks preceding the intervention phase.

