### Outcomes

#### Primary outcome measure

The primary outcome is adherence to immunosuppressive treatments 1 year after transplantation (M12). To assess therapeutic adherence (compliance and persistence), a combination of two methods is recommended [12]. Accordingly, we will use the BAASIS (Basel Assessment of Adherence to Immunosuppressive Medication Scale) questionnaire and the health insurance data from the national health data system (SNDS). The BAASIS questionnaire [13] will be used 1 year after the transplantation (M12) (Additional file 3). This is a recognized questionnaire for assessing adherence to immunosuppressive therapy. It includes 4 questions to determine whether, in the last 4 weeks, the patient forgot to take, did not respect the taking schedule (to the nearest 2 h) or changed the dosage of their immunosuppressive treatment. A patient answering “yes” to one of the 4 questions will be treated as a non-adherent.

Using the SNDS health insurance data, we will verify that over the year following the transplantation, 100% of the days are covered by immunosuppressive drug possession by counting the number of tablets dispensed by the CP during this period (for hospitalization days, therapeutic adherence will be estimated at 100%). The SNDS health insurance data are described in Additional file 4.

To be considered as adherent, a patient must be assessed as an adherent on both criteria.

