### Analysis

Data will be analysed according to a pre-established statistical analysis plan that will be finalized before locking the database. The results of the study will be reported in accordance with the guidelines of the CONSORT Statement extension for the stepped-wedge cluster randomized trials [9]. In accordance with act no. 2002-303 of 4 March 2002, if they request it, the participants will be informed of the results of the study.

Cluster characteristics will be reported using descriptive statistics as will be patient characteristics, which will be reported per arm.

The primary endpoint is binary: patients adhering to their immunosuppressive treatment or not (assessed using the BAASIS questionnaire and health insurance data 1 year after transplantation). It will be analysed using a mixed logistic regression model taking into account a period effect and a cluster random effect. It will also be analysed using a mixed model with an identity link function (still taking into account both time and clustering), thus allowing to estimate a risk difference. All included patients will be taken into account in the main analysis and considered in the group (control or experimental) corresponding to the period during which they have been included, whatever occurred. In case the BAASIS questionnaire is missing, we will consider health insurance data (SNDS data) only to specify whether a patient is adherent or not. Because health insurance data are routinely collected data for all French people, we do not expect any missing data. No subgroup analyses or adjusted analyses are planned.

Binary secondary endpoints (adhesion, graft survival at 1 and 3 years, appearance of HLA antibodies, presence of episodes of acute rejection) will be analysed using the same approach as that used for the primary endpoint. For continuous secondary criteria (knowledge of the patient, patient satisfaction, coefficient of variation of the dosages), a mixed linear model will be used taking into account a period effect and a cluster random effect.

Data will be analysed by statisticians from the CIC Centre INSERM 1415 using SAS or R software.

The cost-utility and cost-effectiveness analyses will follow the French guidelines for economic evaluation in health care.

After the data management of SNDS data by the EpiDclic Unit, the health-economic analysis will be performed by UEME. It will be performed using the following software: Excel, Stata and R.

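### Patients with no BAASIS are classified on SNDS alone, so the primary endpoint has one hurdle for them and two for everyone else

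*Protocol article*

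**What the plan says.** Under Primary outcome measure, the protocol article combines two instruments. SNDS must show that "100% of the days are covered by immunosuppressive drug possession" over the year after transplantation. BAASIS is given once, at M12, and a yes to any of its four questions makes the patient non-adherent. The two are joined strictly: "To be considered as adherent, a patient must be assessed as an adherent on both criteria".

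Under Analysis, the article keeps all included patients in the main analysis, in the group of their inclusion period, and sets the missing-data rule: "In case the BAASIS questionnaire is missing, we will consider health insurance data (SNDS data) only". The next sentence reassures the reader: "Because health insurance data are routinely collected data for all French people, we do not expect any missing data". The reason it gives concerns the insurance data only. The article states no expected BAASIS completion rate.

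Under Control and intervention phase, the trial is described as unblinded for patients and healthcare team. In the intervention phase the hospital pharmacist has extra contact with the patient: "he/she will conduct 3 pharmaceutical consultations with the outpatient 1 month (M1), 3 months (M3) and 12 months (M12) after transplantation".

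**The concern.** A composite that requires two passes becomes a single-pass endpoint for anyone who does not return the questionnaire. A patient who fails SNDS is non-adherent with or without BAASIS, so the rule changes nothing there. For a patient who passes SNDS, it fills the missing BAASIS with a pass. Not answering a self-report adherence questionnaire is no evidence of perfect adherence.

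The effect on each arm's rate is one-sided: apparent adherence can only go up. The effect on the comparison depends on how much BAASIS is missing in each arm and on how far apart SNDS-only and two-criterion adherence lie. If completion differs between control and intervention, a difference can appear when the plan does nothing, or a real one can be shrunk or enlarged. The period effect and cluster random effect in the primary model do not remove missingness that differs by arm.

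This is a rule fixed in the protocol for the primary analysis, not a detail left to the SAP.

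**Working it through.** **Inputs from the article.** Non-adherence 30% against 20%, so P(both) = 0.70 and 0.80; 12 clusters, 11 patients per cluster-period, ICC 0.01, 90% power, N = 1716 (Sample size calculation).

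**Assumed, because the article does not give them.** SNDS-only adherence P(SNDS); the share m with BAASIS missing; BAASIS missing at random within arm; a two-sided 5% test.

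**The plan's own figure.** A stepped-wedge generalised least squares calculation (fixed periods, random cluster, variance equal to the mean of p(1−p) over the arms) with 12 × 13 × 11 = 1716 and no cell dropped gives SE 0.031 and power 0.897, which matches the stated 90%. With 14 periods and each cluster's transition cell dropped, SE is about 0.034 and power about 84%. Both baselines matter for reading power below.

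**Step 1. Inflation within an arm.**

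P(classified adherent) = (1 − m) × P(both) + m × P(SNDS) = P(both) + m × [P(SNDS) − P(both)].

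The added term is never negative. With P(both) = 0.70, it runs from 0.10 × (0.75 − 0.70) = 0.5 points to 0.30 × (0.90 − 0.70) = 6 points.

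**Step 2. No true effect.** With 70% in both arms, the spurious difference is (m_int − m_ctrl) × [P(SNDS) − 0.70]. The rejection rate is Φ(−1.96 + d/SE) + Φ(−1.96 − d/SE), with SE from the 13-period calculation at the classified rates.

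| Assumed P(SNDS) | 20% ctrl / 10% int | 30% ctrl / 10% int | Rejection rate at 30/10 |
|---|---|---|---|
| 0.72 | −0.2 points | −0.4 points | 5.2% |
| 0.75 | −0.5 | −1.0 | 6.1% |
| 0.80 | −1.0 | −2.0 | 9.5% |
| 0.85 | −1.5 | −3.0 | 15.5% |
| 0.90 | −2.0 | −4.0 | 24.5% |

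Reversing the missing shares reverses the sign and keeps the size.

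**Step 3. True 70% against 80%, equal missingness.** The classified difference is (1 − m) × (difference on both criteria) + m × (difference on SNDS). It shrinks only if the SNDS difference is smaller than the composite difference. Two splits that give the same 70% and 80%, with m = 20%:

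- SNDS 87.5% against 91.7%: 0.8 × 10 + 0.2 × 4.2 = 8.8 points.
- SNDS 80% against 91.4%, with 87.5% of SNDS-adherent patients passing BAASIS in both arms: 0.8 × 10 + 0.2 × 11.4 = 10.3 points.

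Power for 8.8 points: the SE implied by 90% power is 0.10 / (1.960 + 1.282) = 0.0308, so Φ(0.088/0.0308 − 1.96) is about 82%, against 90%. With SE 0.034 it is about 74%, against 84%.

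**Step 4. True 70% against 80%, missing 30% control / 10% intervention.**

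- SNDS 75% control, 80.2% intervention: control 0.70 + 0.3 × 0.05 = 0.715; intervention 0.80 + 0.1 × 0.002 = 0.800; difference 8.5 points, power about 79%.
- SNDS 90% control, 96.2% intervention: control 0.70 + 0.3 × 0.20 = 0.760; intervention 0.80 + 0.1 × 0.162 = 0.816; difference 5.6 points, power about 48%.

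These powers start from the 0.897 baseline. With 10% / 30% missing, the differences are 9.6 and 12.9 points.

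**The case against.** The strongest reply is that nothing in the article shows BAASIS completion will differ by arm. The pharmacist consultation is placed alongside the M12 medical visit, which is not described as specific to one arm. EQ5D-5L is collected at M12 without restriction by arm, by phone if needed, and no text says the pharmacist administers BAASIS. This stands: unequal completion is plausible in an unblinded trial with extra M12 contact in one arm, but a reader who infers that it is likely goes beyond the document.

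Second, the SNDS criterion is strict. If most patients with every day covered also pass BAASIS, P(SNDS) is close to P(both) and the bias nearly vanishes, as the first row of the table shows. This also stands.

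Third, a reader might infer that equal missingness always dilutes the effect. It does not, as the 10.3-point example shows. That case is not far-fetched, because the pharmacist's call to the community pharmacist about possession acts on the SNDS component. A reader might also set 74% power against the planned 90%. That comparison is wrong, because about 6 of those 16 points are already lost at SE 0.034 with no missing BAASIS.

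Fourth, more contact at M12 in the intervention arm would most naturally leave more BAASIS missing among controls, which works against the intervention. The document offers no mechanism for the opposite pattern.

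Finally, imputation under missing at random does not cure informative non-response. That is right, and is why sensitivity analyses are needed. None of these points defends a rule that gives responders and non-responders different definitions of the endpoint.

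**Conclusion.** The inconsistency is real. The two-criterion definition and the missing-data rule do not describe the same endpoint, and the statement that no missing data are expected does not cover BAASIS. Whenever BAASIS is missing for patients who pass SNDS, adherence is overstated unless all of them would have passed the questionnaire.

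The size for the comparison cannot be read from the document. Over the assumed range P(SNDS) = 75–90% and missing shares of 30% and 10%, the spurious difference is 1 to 4 points in either direction, against a planned difference of 10. It is under half a point at P(SNDS) = 72%. The document does not support a claim that the trial will be biased in a known direction, or that the effect must be diluted. Because the importance depends on unknown missingness, this is a should-fix.

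**What to change.** Replace the rule for the primary analysis, before database lock:

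- Classify SNDS-non-adherent patients as non-adherent whatever BAASIS shows or whether it is present.
- For SNDS-adherent patients with no BAASIS, multiply impute the BAASIS result from arm, period, cluster, organ, SNDS data and baseline variables, adding EvalOBS where available. EvalOBS is itself patient-reported at M12 and will often be missing with BAASIS, so the model should not depend on it.
- State how patients who die before M12 are classified. They have no BAASIS, yet all included patients enter the main analysis.
- Because non-response may be informative, keep two sensitivity analyses: SNDS only, and missing counted as non-adherent. They bound adherence within each arm; crossing them between arms bounds the difference.
- Report the share with missing BAASIS by arm.

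If BAASIS is missing at random given the imputation variables, this recovers the two-criterion endpoint. The cost is some extra analysis work and no new data. Because the present rule is in the protocol, the change may need the amendment route described under Funding source and regulatory aspects.

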## Methods/design

### Study design and randomization procedure

This study will be a stepped-wedge cluster randomized trial. Clusters will be 12 transplantation units. In cases where a hospital has both a kidney and liver transplant unit, these units will correspond to two clusters. However, if both kidney and liver transplant patients are managed within the same transplant unit, this latter unit will be considered as a single cluster. In a stepped-wedge trial, all centres start the study on the same day in the control phase. Then, one after the other, at regular time intervals, each cluster will switch to the intervention phase and remain there until the end of inclusions. During the control phase, the practices of the different centres will not be modified. During the intervention phase, the PPP will be deployed.

In order to gain power, there will be as many sequences (and therefore switch dates) as clusters, meaning that only one cluster at a time will switch from the control phase to the experimental phase. A 7-week transition period will take place at the beginning of all intervention phases, such that the intervention can be rolled out under optimal conditions. The clusters will all be randomized at the beginning of the study and cluster gatekeepers informed of the randomization result. Because some centres had to recruit staff to carry out the intervention phase, communication of the randomization result is mandatory. Randomization will be managed by the biostatistician of the study at the Clinical Investigation Centre (CIC) INSERM 1415. The patient recruitment period will last 23 months with a 3-year follow-up (Fig. 1).

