### Clusters and participants

In total, this study will bring together 12 clusters (5 liver clusters, 6 kidney clusters and one mixed cluster) representing 10 French university hospitals (Brest, Marseille, Montpellier, Nantes, Poitiers, Strasbourg, Reims, Rennes, Toulouse and Tours).

Inclusion criteria are as follows: be 18 years old or older; have given their free, informed and express consent; speak French; live in France and have no plan to move for the duration of the study; declare going to the same community pharmacy each time (in France, 81% of French people declare themselves loyal to their community pharmacy [9]); and be health-insured.

Protected patients (safeguard of justice, curatorship or tutorship), already transplanted (whatever organ) or having benefited from a double transplantation (kidney/heart, kidney/liver with a centre not participating in the study or liver/heart) will be excluded.

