### Recruitment and inclusion

Patients will be recruited postoperatively as soon as they will be able to understand the purpose of the research. Provided consent is given, all transplant patients meeting the inclusion criteria will be included in the study. The investigator of the centre will ensure the information and collection of the patient’s consent.

Patients are expected to be loyal to a community pharmacy. Consequently, any pharmacy may be involved in this present study. All community pharmacists (CP) will be informed of the study in three ways: a professional journal supported by the pharmacist union, a professional journal supported by the national council of the order of pharmacists and a letter sent by the study scientific committee distributed by wholesale drug distributors. CP having at least one patient included in this study will be informed of the study and the inclusion of their patient by hospital pharmacists. They will be given explanations on the study, how to use the tools and their key role.

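### Ruling out every adjusted analysis gives up some precision and leaves a change in case mix between phases without any model term

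*Protocol article*

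**What the plan says.** The protocol article, section Analysis, fixes the primary analysis as a "mixed logistic regression model taking into account a period effect and a cluster random effect", with a companion identity-link model for the risk difference. It then closes the covariate question: "No subgroup analyses or adjusted analyses are planned". This is a stated decision, so a statistical analysis plan that follows the article cannot add covariates.

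Four other statements bear on it:

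- Clusters and participants: there are "12 clusters (5 liver clusters, 6 kidney clusters and one mixed cluster". In the mixed unit, organ varies between patients within one cluster, because "if both kidney and liver transplant patients are managed within the same transplant unit, this latter unit will be considered as a single cluster" (Study design and randomization procedure).
- Study design and randomization procedure: "The clusters will all be randomized at the beginning of the study and cluster gatekeepers informed of the randomization result".
- Recruitment and inclusion: "Patients will be recruited postoperatively as soon as they will be able to understand the purpose of the research". The centre's investigator gives the information and takes consent. The same section says that every eligible patient who consents is enrolled.
- Control and intervention phase: neither patients nor the care team can be blinded.

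Patient characteristics are to be reported per arm, descriptively only (Analysis).

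**The concern.** Two separate things are left out of the model.

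The first is organ. With one cluster per sequence, the split of liver and kidney patients between control and intervention depends on the order drawn. At a low intraclass correlation (ICC), a random-intercept model still takes information from comparisons between clusters. Part of any liver-kidney difference in adherence therefore enters the estimate for that order.

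The second is patient mix. Consent is sought after the unit's phase is known, by staff who are not blinded, so those who are approached or agree could differ between the two phases of the same unit. A random cluster effect cannot absorb a change inside a cluster, and a common period effect removes only trends shared by all clusters.

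At stake are some precision, a chance imbalance that could be corrected, and the lack of any prespecified answer if the per-arm table shows imbalance.

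**Working it through.** **Inputs from the article (Sample size calculation).** Non-adherence 30% against 20%; 12 sequences of one cluster; fourteen 7-week periods, one of them a transition; 11 patients per cluster-period; ICC 0.01; power 90%; total 1716. **Assumed, because the article gives no figure:** two-sided alpha 0.05 and every liver-kidney adherence gap below.

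**Method.** Linear mixed model with fixed periods and a random cluster effect, fitted by generalised least squares. Within cluster k, V_k = [σ²(1−ρ)/m]·I + ρσ²·J, with σ² = 0.25 × 0.75 = 0.1875 and m = 11. Var(θ) is the treatment element of (Σ Z_k′V_k⁻¹Z_k)⁻¹. Power = Φ(0.10/SE − 1.96).

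**1. The stated 90%.** Two layouts analyse 12 × 13 × 11 = 1716 patients.
- 13 periods without a transition gap: SE 0.0312, Φ(0.10/0.0312 − 1.96) = 89.3%, close to the stated figure.
- 14 periods with each transition cell dropped: SE 0.0340, Φ(0.10/0.0340 − 1.96) = 83.7%.

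The article does not settle which layout applies, so both are carried forward.

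**2. What organ could add to the ICC.** Code liver 0, kidney 1 and the mixed unit 0.5. The mean is 6.5/12 = 0.5417 and the variance is 6.25/12 − 0.5417² = 0.2274. For a gap d, the between-cluster variance is 0.2274·d².
- d = 5 points: 0.2274 × 0.0025 / 0.1875 = 0.003.
- d = 10 points: 0.2274 × 0.01 / 0.1875 = 0.012.

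Added to 0.01, the 10-point gap gives about 0.022; 0.0225 is used below.

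**3. Power with organ left out, gap 10 points.**

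| Layout | ICC 0.01 | ICC 0.0225 | Loss |
|---|---|---|---|
| Transition cell dropped | 83.7% (SE 0.0340) | 79.7% (SE 0.0358) | 4.0 |
| No gap | 89.3% | 86.0% | 3.3 |

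**4. Shift in one realised switch order, gap 10 points, transition cell dropped.** The estimation weights are applied to organ alone over random orders. The mean is zero.
- ICC 0.0225, which matches the assumed data: SD about 1.0 point.
- Weights fixed at ICC 0.01: SD 1.5 points, largest seen 4.5.
- ICC 0.05: SD about 0.5 points.

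At ICC-0.01 weights, gaps of 5, 15 and 20 points give SDs of 0.8, 2.3 and 3.0.

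**5. The shift is already in the standard error.** At ICC 0.0225 the shift makes up about 1.0²/3.6² = 8% of the squared SE. It must not be added to the power loss in step 3.

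**6. What adjustment does, transition cell dropped.** If the 10-point gap exists, adding organ raises power from 79.7% to about 83%, most of the 4.0 points lost. If organ has no effect, adding it lowers power from 83.7% to about 83%, roughly 1 point.

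**7. Patient mix.** Suppose the share of some patient type changes by s at every cluster's switch, and that type's adherence differs by g. The estimate is then biased by s × g in full, because neither period nor cluster terms absorb it. With s = 10 and g = 20 points the bias is 0.10 × 0.20 = 2 points. Type I error becomes Φ(0.02/0.034 − 1.96) + Φ(−0.02/0.034 − 1.96) = 9%. Over s = 5 to 20 and g = 10 to 30 points, the bias runs from 0.5 to 6 points and type I error from about 5% to 42%. These figures illustrate sensitivity; they do not estimate what will happen.

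**The case against.** A prespecified model with period and cluster alone is a recognised, valid analysis. The switch order is randomised, and organ is constant in 11 of the 12 clusters, so the random cluster effect already models most of it. All of this stands. A reader might infer that leaving organ out biases the effect in a predictable direction. The documents do not support that: the mean shift over switch orders is zero.

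The organ gap is assumed, and the planned ICC of 0.01 may already contain organ variation, in which case step 2 adds nothing to it. This also stands. Organ alone would exceed the planned ICC only at a gap near or above 10 points (9.1 by √(0.01 × 0.1875/0.2274)); at 5 points it contributes 0.003.

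The article describes no organ stratification of the order, but silence in a condensed article is not a defect and is not counted as one.

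On recruitment, a reader might infer that investigators will select by phase. No statement in the article shows this. Enrolling all eligible consenting patients limits the scope for it, and the per-arm table would show an imbalance in the reported characteristics. But consent is itself the exposed step, and seeing an imbalance is not the same as having a planned analysis for it. It is also fair that selection would more plausibly act through motivation or expected adherence, which organ, age and sex capture only in part.

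**Conclusion.** The concern holds at a modest size. The article expressly excludes a low-cost safeguard that its own design calls for.

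For organ, the loss is precision and protection against chance imbalance: 3 to 4 points of power and an SD of about 1.0 point in the realised estimate, against a 10-point target and an SE of about 3.6 points. This rests on an assumed 10-point gap lying on top of the planned ICC; at smaller gaps it shrinks quickly.

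For patient mix, the gap in the model is real because no term addresses a within-cluster change between phases. Its size is unknown, and no differential recruitment has been shown. The exclusion of subgroup analyses is not at issue.

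**What to change.** Before database lock, replace the sentence excluding adjusted analyses. Prespecify a model with organ transplanted (kidney or liver, recorded per patient so that the mixed unit is handled), age and sex as fixed effects besides treatment, period and the random cluster effect. Report it alongside the model without covariates, and state in advance which of the two is primary.

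Take the covariates from the trial's own baseline records. The table of birth dates and sex described under Data management goes to an independent third party for SNDS linkage and is not an analysis source.

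The change is one of wording; the Analysis section says the analysis plan is finalised before the database is locked. Its costs are:

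- about 1 point of power if organ is not prognostic;
- an odds ratio that is conditional on the covariates, and so not directly comparable with the one from the model without them;
- possible convergence trouble in the identity-link model.

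Adjustment will only partly address selection through motivation or expected adherence, and the report should say so.
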